**Methods:**

This is an open-labeled randomized superiority multicenter phase III trial. Patients with up to 3 bone-only metastases will be randomized in a 1:1 ratio.between Arm A (Experimental group): Standard care of treatment & SBRT to all bone metastases, and Arm B (Control group): standard care of treatment.

For patients receiving SBRT, radiotherapy dose and fractionation depends on the site of the bone metastasis and the proximity to critical normal structures. This study aims to accrue a total of 196 patients within 4 years.

The primary endpoint is progression-free survival at 1 year, and secondary endpoints include Bone progression-free survival; Local control; Cancer-specific survival; Overall survival; Toxicity; Quality of life; Pain score analysis, Cost-utility analysis; Cost-effectiveness analysis and Budget impact analysis.

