### Evaluation and randomization

Prior to randomization, a complete history and physical examination is required. Histologically confirmation of malignancy is required, with metastatic disease detected on imaging.

The mechanism of implementing the allocation sequence (stratified randomization) is generated by computer. Clinical research assistant generate the allocation sequence and physician enroll and assign participant to intervention.

Patients must be restaged within 6 weeks before randomization, including brain CT or MRI and CT-TAP. For all patients with a suspicion of spinal bone metastases, a spinal MRI is mandatory.

The patients will also benefit from PET-CT exams before treatment. PET1 F-Choline, NaF and FDG are standard examinations for metastases staging; and PET2 FDG or F-Choline for evaluation. If NaF-PET cannot be done, patients will have a “conventional” biphosphonates SPECT-CT with a tomographic exploration from the vertex to mid-thigh in double or triple field instead.

Patients with prostate cancer are also required to have PSA blood test. A negative pregnancy is required for women of child-bearing age (Table 1).

**Table 1 Tab1:** Timeline and follow up of the study

	Screening	Randomization	Treatment	Follow up				
				M3	M6	Y1	Y2	Y3
**History & physical**	X		X	X	X	X	X	X
**Brain CT or MRI**	X				X	X	X	X
**TAP CT**	X				X	X	X	X
**FDG PET or F-Choline PET**	X					X		
**PET or SPECT-CT**	X					X		
**Spinal MRI (if spinal bone metastases)**	X				X	X		
**Mammography (breast cancer)**	X				X	X	X	X
**Histological confirmation**	X							
**Quality of Life**	X		X	X	X	X	X	X
**Toxicity Assessment**			X	X	X	X	X	X
**Pain Assessment**	X		X	X	X	X	X	X
**Economic Study**			X	X	X	X	X	X
**sCTX/ bALP Evaluation**	X		X	X	X	X		

*MRI* Magnetic Resonance Imaging; *TAP-CT* Computed tomography thorax-abdomen-pelvis; *FDG-PET* Fluorodesoxyglucose-Positron Emission Tomography; *F-Choline-PET* Fluor-Choline-Positron Emission Tomography; *PET* Positron Emission Tomography; *SPECT-CT* Single Photon Emission Tomography-Computed Tomography; *sCTX* serum C-Telopeptide cross-link of type 1 collagen; *bALP* bone ALkaline Phosphatase

The present research project will be developed for 48 months, during which specific milestones will be achieved and documented (Table 1).

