### Statistical analysis

Sample size calculation: 196 patients will be randomized between 2 arms (in a 1:1 ratio). The primary endpoint is the 1-year Progression Free Survival (PFS). In the standard arm, the expected progression-free survival at 1 year is 30% (10% for lung cancer, 50% for breast cancer and 30% for prostatic cancers). In the experimental arm, we anticipate a 20% absolute increase (i.e. 30, 70 and 50%, respectively). According to Freedman’s method, accepting a two-tailed type I error of 5% and an 80% power (type II error of 20%), 178 patients (2 X 89) need to be recruited and 106 events need to be observed for the primary analysis. Assuming a 10% withdrawal rate, a total of 196 patients will need to be included.

Data analysis: All patients will be randomized after completion of the primary tumor treatment for synchronous or metachronous metastasis. The randomization will be stratified by date of metastasis (synchronous vs. metachronous) and primary tumor site (breast vs. non-small cell lung vs. prostate cancer). Statistical analysis will be performed on all the randomized patients, accordingly to the intent to treat (ITT) arm, whatever the actually received treatment. Patients without progression and alive at the time of analysis will be censored at the time of the latest assessment.

Primary Endpoint Analysis: Progression Free Survival PFS is defined as the time from randomization until the date of the first objective progression accordingly to RECIST or death (whatever its cause in the absence of progression). Patients without progression and alive at the time of analysis will be censored at the time of the latest assessment. The primary analysis will take place when 106 events have been observed. This analysis will use the logrank test, stratified on the primary location and the time of onset of the bone metastases (synchronous vs metachronous). Cox regression model will also be used to perform a sensitivity analysis taking into account the usual prognostic factors. The hazard ratio will be given with its 95% confidence interval. A *p* value <= 0.05 will be considered as statistically significant. A secondary analysis will also be performed, using the Fine and Gray model in order to take into account the competing risks (relapse in the bone, relapse in another site, death), and so to analyse the impact of the different PFS events on the trial results.

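### The 106-event trigger carries no accrual or follow-up condition, so the 1-year PFS readout may come during recruitment, although log-rank power is intact

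*Protocol article*

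**What the plan says.** All references are to the protocol article.

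- **Endpoint.** The Abstract, Primary endpoint and Statistical analysis sections name PFS at 1 year. The definition is not cut off at 12 months: "Progression Free Survival PFS is defined as the time from randomization until the date of the first objective progression accordingly to RECIST or death".
- **Size.** "In the standard arm, the expected progression-free survival at 1 year is 30" per cent. "In the experimental arm, we anticipate a 20% absolute increase". By Freedman's method, with a two-sided 5% error and 80% power, "178 patients (2 X 89) need to be recruited and 106 events need to be observed for the primary analysis". A 10% withdrawal allowance brings the total to 196.
- **Analysis.** Stratified log-rank test with a hazard ratio, on all randomised patients by assigned arm.
- **Timing.** "The primary analysis will take place when 106 events have been observed". No minimum follow-up and no end-of-accrual condition is attached to that sentence.
- **Calendar.** The Abstract says "This study aims to accrue a total of 196 patients within 4 years". Evaluation and randomization says "The present research project will be developed for 48 months". Table 1 and the Follow-up section run visits to year 3.

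**The concern.** The 106 events equal the number expected when 178 patients have each been followed for one year. An event-count trigger under staggered entry works differently: early patients go on contributing events after month 12, so the count is reached before late patients have a year of follow-up, and perhaps before they are enrolled.

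Three things are at stake.

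- The trial is open-label. A final comparison released during accrual could influence later enrolment and management, and the article does not say what happens to patients randomised afterwards.
- Analysing all randomised patients, planned as 196, does not fit a cutoff at which some are not yet randomised.
- The endpoint carries a 12-month label, and Table 1 schedules the post-baseline PET or SPECT-CT only at 1 year. Patients short of month 12 will not have had it.

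**Working it through.** **1. The plan's own figures.** HR = ln(0.50)/ln(0.30) = 0.576. Freedman events = [(1 + 0.576)/(1 − 0.576)]² × (1.960 + 0.842)² = 108.3, against 106 stated (within 3%). Mean 1-year PFS is (30% + 50%)/2 = 40%, so 178 × 0.60 = 106.8 events if all 178 are followed for 12 months. Inflation: 178 × 1.10 = 196. The figures reproduce.

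**2. When the 106th event arrives.** From the article: 196 patients, 1:1, 48 months of accrual, 1-year PFS 30% v 50%. Assumed: uniform entry, exponential PFS, no loss. Monthly hazards are λ = −ln(0.30)/12 = 0.1003 and −ln(0.50)/12 = 0.0578. For T up to 48 months, expected events per arm = (98/48) × [T − (1 − e^(−λT))/λ]. At T = 38.6:

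- control: 2.042 × (38.6 − 9.76) = 58.9
- experimental: 2.042 × (38.6 − 15.45) = 47.3
- total: 106.1

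At that date 196 × 38.6/48 ≈ 157 are randomised and 196 × 26.6/48 ≈ 109 have 12 months of potential follow-up. About 49 (31% of those randomised) do not. Using the article's tumour-specific rates in equal thirds moves the date to month 39.1, with 160 randomised.

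**3. Sensitivity (196 patients).**

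| Assumption | Month of 106th event | Randomised | Under 12 months, of those randomised |
|---|---|---|---|
| Uniform 48 months, no loss | 38.6 | 157 | 31% |
| Uniform, 10%/year loss | 40.5 | 165 | 30% |
| Uniform, events found only at scheduled scans | 43.1 | 176 | 28% |
| Uniform, scans plus 10%/year drop-out (simulated) | 46–47 | 189 | 25% (48 of 189) |
| Back-loaded 48 months | 43–50 | 169–196 | 35–45% |

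A separate set of simulated ramped-accrual scenarios put the trigger at months 44 to 52. With 24-month accrual it falls at months 24 to 28, at or after the end of recruitment.

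**4. Power of the planned test.** By Freedman's formula, power = Φ(√d × 0.424/1.576 − 1.96). For d = 106 this is 79%. Simulation gives 0.80 to 0.81.

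**5. Precision at 12 months.** At month 60 (48 + 12), without loss, everyone has a year of follow-up: 1.96 × √[(0.30 × 0.70 + 0.50 × 0.50)/98] = 13.4 points. At month 38.6, Greenwood's variance with (98/48) × (38.6 − u) × S(u) at risk per arm at follow-up time u gives 16.6 points, against a 20-point target difference.

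**6. Effect of waiting.** At month 60 the simple no-loss model gives 92.0 + 81.4 = 173 events. Scenarios with scan-based detection and drop-out give 131 to 168. Freedman power is 87% at 131 events and 94% at 168.

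**7. Calendar.** If accrual takes 48 months, the last patient reaches month 12 at study month 60 and month 36 at study month 84. Neither fits a 48-month project.

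**The case against.** A reader might infer that the trial cannot answer its primary question at the stated power. The document does not support that. The 80% belongs to an event-driven log-rank test, whose power depends on the number of events and is about 80% at 106. A power of about 65% does arise for a Kaplan-Meier comparison at 12 months at that cutoff, but no such test is planned. Censoring deals with incomplete follow-up, and a 1-year estimate can still be obtained.

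The shortfall should not be overstated either. Taken over all 196 it includes people not yet enrolled. Some patients short of 12 months have already progressed or died: in the base case only about 32 of 157 (20%) are both event-free and under 12 months.

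Whether the trigger precedes the end of recruitment depends on accrual shape and event detection, which the article does not give, and within 4 years is an upper bound. The sentence "178 patients (2 X 89) need to be recruited and 106 events need to be observed for the primary analysis" can also be read as a joint condition on recruitment and events. Finally, waiting buys more log-rank power than the 80% chosen, at the price of a later result.

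All of this stands. It does not remove the point: the timing sentence itself names only the event count, and even the joint reading sets no follow-up condition for an endpoint labelled 1-year PFS.

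**Conclusion.** The concern holds as a timing and consistency defect, not as a loss of power. With uniform 48-month entry and exponential PFS at the plan's rates, the trigger is expected at about month 39, or 43 to 47 with scan-based detection, without or with drop-out. At month 39 about 157 to 160 of 196 are randomised and about 30% of those have under 12 months of potential follow-up. Under faster or back-loaded accrual it can fall at or after the end of recruitment, so a readout during recruitment is likely on the base assumptions but not certain. The 12-month difference is estimated to about ±16.6 points instead of ±13.4.

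Separately, a 48-month project, 4 years of accrual and 3 years of follow-up cannot all hold if accrual takes the full 4 years. This is a cheap and worthwhile correction; the planned primary test remains valid without it.

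**What to change.** Replace the timing sentence with: *The primary analysis takes place when at least 106 events have been observed, accrual is complete and the last randomised patient has reached the 12-month assessment. No final efficacy comparison is released before then; DSMC reviews are exempt.* Restate the expected events (about 130 to 170, depending on drop-out and detection) and log-rank power (about 87 to 94%).

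In the same amendment, say what the 48 months cover, and reconcile them with the accrual period in the Abstract and the year-3 visits in Table 1 and Follow-up.

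The cost is a later readout: against triggers at months 39 to 52, month 60 is roughly 8 to 21 months later. No extra patients or visits are needed, because follow-up to year 3 is already planned.

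### The article names only Fine-Gray to explain which PFS events drive the result, but a subdistribution hazard ratio alone cannot attribute the effect to an event type

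*Protocol article*

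**What the plan says.** The Primary Endpoint Analysis paragraph of the Statistical analysis section sets out three analyses of PFS:

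- a logrank test stratified by primary site and by synchronous or metachronous onset;
- a Cox model adjusted for prognostic factors, as a sensitivity analysis, not described as cause-specific;
- a secondary analysis "using the Fine and Gray model in order to take into account the competing risks (relapse in the bone, relapse in another site, death").

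The aim of the third is stated: "so to analyse the impact of the different PFS events on the trial results". The article therefore fixes both a method and the question it is meant to answer.

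The Secondary endpoints section defines bone progression-free survival over the whole skeleton, without naming a model for it. It defines no matching endpoint for non-bone relapse. The Background bases the expected PFS gain on better local control in bone. The article gives no expected split of PFS events by type.

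**The concern.** Asking how much each event type contributes to the PFS effect means splitting the PFS hazard by cause. Cause-specific hazards do this, because they add up to the PFS hazard. Subdistribution hazards do not, because patients who have had a competing event stay in the risk set. If SBRT prevents bone relapses, more SBRT patients remain available to have a first relapse elsewhere. The Fine-Gray ratio for non-bone relapse then rises even though the rate among patients still event-free is the same in both arms.

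The ambiguity thus arises when the trial's own hypothesis is true. A ratio above 1 for non-bone relapse could mean a higher relapse rate, or only that fewer patients had a bone relapse first. Fine-Gray output alone does not separate the two.

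**Working it through.** **Inputs from the Statistical analysis section.** One-year PFS is 30% in the control arm and 50% with SBRT; two-sided 5% error; 80% power; 1:1 allocation; "178 patients (2 X 89) need to be recruited and 106 events need to be observed for the primary analysis".

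**Reproducing the plan's figure.** With exponential PFS, the hazards are -ln(0.30) = 1.204 and -ln(0.50) = 0.693 per year, so HR = 0.693/1.204 = 0.576. Freedman: events = (1.960 + 0.842)² x [(1 + 0.576)/(1 - 0.576)]² = 108.3. Patients = 2 x 108.3/(2 - 0.30 - 0.50) = 180.4. Both agree with 106 and 178 to within 3% (an HR rounded to 0.572 gives 106). If all 178 were followed for one year, 178 x (0.70 + 0.50)/2 = 106.8 events would be expected, so one year of follow-up for everyone is a fair stand-in for the event trigger.

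**Assumptions not in the document.** Hazards are constant. Bone is 45-80% of the control PFS hazard. Death is 10% of the remainder. The whole PFS gain falls on bone, and the non-bone relapse and death hazards are the same in both arms. The true cause-specific HR for non-bone relapse is therefore 1.00.

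**Worked example, 60% bone share.** Control hazards: bone 0.60 x 1.204 = 0.722; other site 0.9 x 0.40 x 1.204 = 0.433; death 0.048. With SBRT, bone falls by 1.204 - 0.693 = 0.511 to 0.212 (bone HR 0.293); the others do not change. One-year cumulative incidence = (cause hazard/total hazard) x (1 - PFS):

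| First event | Control | SBRT | Cause-specific HR |
|---|---|---|---|
| Bone relapse | 0.722/1.204 x 0.70 = 42.0% | 0.212/0.693 x 0.50 = 15.3% | 0.293 |
| Other-site relapse | 0.433/1.204 x 0.70 = 25.2% | 0.433/0.693 x 0.50 = 31.3% | 1.00 |
| Death | 0.048/1.204 x 0.70 = 2.8% | 0.048/0.693 x 0.50 = 3.5% | 1.00 |

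The columns sum to 70% and 50%, to rounding. Other-site relapse as a first event rises by 6.1 points with no change in its rate.

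**Size of the Fine-Gray ratio.** It was fitted to 300,000 simulated patients per arm with administrative censoring only. Trial-size behaviour comes from 2,000 simulated trials of 2 x 89. All figures are for other-site relapse at one year:

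| Bone share | Implied bone HR | Incidence, control vs SBRT | Fine-Gray ratio | Estimate above 1 | Significant increase |
|---|---|---|---|---|---|
| 45% | 0.057 | 34.6% vs 43.0% | 1.29 | 85% | 18% |
| 60% | 0.293 | 25.2% vs 31.3% | 1.27 | 82% | 12% |
| 80% | 0.470 | 12.6% vs 15.6% | 1.24 | 70% | 7% |

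At 60% share, 95% of trial-size estimates lie between 0.74 and 2.32.

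**Other bone effects.** With bone HRs of 0.3-0.7 and bone shares of 30-70%, the one-year ratio is 1.06-1.32. The top value (70% share, HR 0.3) implies 54% PFS with SBRT, slightly more than planned; without that cell the maximum is 1.28. With no bone effect the ratio is 1.01, which is 1 within simulation error.

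**Longer follow-up.** If every patient were followed for three years, an upper bound, the ratio is 1.60-1.83 and a significant increase appears in 31-87% of trials.

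**Cause-specific Cox model on the same data.** The HR for other-site relapse is 0.99-1.00 at every setting. A significant increase appears in 1.5-2.9% of trials, about the nominal one-sided rate.

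**The case against.** The strongest reply has four parts.

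- **The article condenses the full plan.** A reader might infer that no other competing-risk model is planned. That cannot be known, because the analysis plan is not shown. What can be said is that Fine-Gray is the only one this article names. The point survives because the article also states the question Fine-Gray is to answer, and that pairing does not fit.
- **Fine-Gray is not wrong.** One minus PFS is the sum of the cumulative incidences, and those are what Fine-Gray models. In the example, first relapses at other sites really do become more frequent. This stands: the ratio is a valid description of absolute risk. It cannot by itself say which event rate SBRT changed.
- **The scenario is favourable to the concern.** The bone share is assumed, and a 45% share requires SBRT to abolish nearly all bone relapse across the skeleton (HR 0.057). This stands as a limit on the size. Nor does the article say that SBRT leaves non-bone relapse unchanged. If SBRT lowered that too, the Fine-Gray ratio would mix a real reduction with the upward shift, and cause-specific ratios would still be needed to separate them.
- **Misreading is not certain.** All three event types are listed, so a fall in bone relapse would be visible beside any rise elsewhere, and bone progression has its own endpoint. This lowers the risk but does not remove it, since non-bone relapse has no endpoint of its own.

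**Conclusion.** The point holds as a mismatch between method and stated aim in a secondary analysis. Under the trial's hypothesis, and with an unchanged non-bone relapse rate, the Fine-Gray ratio for non-bone relapse is expected to be about 1.24-1.29 at one year when the whole PFS gain falls on bone (assumed share 45-80%), about 1.06-1.32 over the wider grid, and about 1 if SBRT does not affect bone relapse.

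Three stronger readings are tempting and are not supported:

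- **That the analysis will show an apparent increase.** This depends on SBRT lowering bone relapse. Even then, 15-30% of trials of the planned size would give an estimate at or below 1 at one year.
- **That a significant apparent harm is likely.** At one year this occurs in 7-18% of simulated trials. The larger figures belong to the three-year upper bound.
- **That the trial's main conclusion is at risk.** The stratified logrank test, the event trigger and the sample size are untouched.

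The direction follows from how the subdistribution risk set is defined. The size rests on constant hazards and on an event split that the document does not give.

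**What to change.** In the Primary Endpoint Analysis paragraph of the Statistical analysis section:

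1. Add cause-specific Cox models for bone relapse, other-site relapse and death, stratified by the two randomisation factors (primary site; synchronous or metachronous onset), and name them as the analysis that attributes the PFS effect to event types.
2. Show cumulative incidence curves by arm for every event type.
3. Keep Fine-Gray as the companion description of absolute risk, and state that its ratio for one event type also reflects effects on the others.

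The cost is a few lines of text and code, with no new data. The downside is imprecision for the rarer events. At one year the simulated trials contain on average about 25 to 69 other-site relapses. In the 60% example only about 89 x (0.028 + 0.035) = 5.6 deaths would be first events, so that model would say little. The results should be presented as estimates with confidence intervals rather than as tests.

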### Data safety monitoring committee

An Data Safety Monitoring Committee (DSMC), with expertise and experience in the pathology, and without direct involvement in the conduct of the trial, will be set up specifically to guarantee effective protection of patients, insure the ethical conduct of the trial, benefit/risk ratio of the trial, and to ensure the independent review of the scientific results during the trial and at the end of the trial. The DSMC will meet after 60 patients are accrued in the experimental arm to review toxicity outcomes and compliance.

The DSMC may recommend the early termination of the trial if one of the following conditions is met: an unacceptable toxicity or all available data from the trial or any other source of information are sufficiently convincing to influence the therapeutical practices of the majority of clinicians. The DSMC has only a consultative role; it will inform the sponsor who will decide whether the DSMC recommendation will be followed. An adverse event (AE) is defined as any untoward medical occurrence, in a patient or clinical trial subject treated by a medicinal product and which does not necessarily have a causal relationship with this treatment. The assessment of whether there is a reasonable causal relationship is made by the investigator. Notification must be carried out immediately by fax to the R&D UNICANCER pharmacovigilance unit by sending the form “notification of a Serious Adverse Effects”, located in the Investigator Master File, completed as precisely as possible, dated and signed by the physician-investigator.

### Biological ancillary study

The follow-up of bone metastasis evaluation is difficult by means of anatomic imaging (CT-scan). There is a need to identify biologic markers that would predict bone disease progression (DP) and risk of skeletal-related events (SREs) as sequelae of bone metastases. As this ancillary study, we have chosen to explore s-CTX and bone alkaline phosphatase (b-ALP) to better quantify response to SBRT vs standard treatment [20–22]. Predictive value of these biomarkers at different points will be assessed on disease control rate (DCR) [23–26]. To perform this study, blood samples (sCTX and bALP: 7 ml in a dry tube will be collected before the beginning of treatment, at the end of treatment, at 3 months, 6 months and 1 year after randomization.

